### Sample's size calculation

We estimated the size of the groups based on two criteria: (1). A review of previous studies showed a mean group size of 34.8 participants and a median of 26 in similar studies in children [30]. (2) The G-Power projection suggested a group size of 22 children for a total sample of 44 children. Table 2 contains the parameters for the calculation of the sample.

**Table 2 tbl0002:** Parameters for the size of the groups.

Parameter	Value	Description
Effect size	0,25 – 0,5	Data based on reports from previous studies.
α error confidence level	0,05	
Sample power	0,95	
Number of groups	2	1 experimental group and 1 TAU control group
Number of measures	3	Pretest, posttest, follow-up
Sample size	N= 22 per group	N=44 full sample

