**Table utbl0001:** 

Subject Area:	• Cognitive sciences
More specific subject area:	• Children's Cognitive Development
Protocol name:	Effect of COGNI-MACHINE computational thinking training on executive functions in children aged 9 to 11: Protocol of a Cluster Randomized Controlled Trial
Reagents/tools:	• Cogni-Machine computational thinking training • Micro:bit based robotics kit • Code.org courses
Experimental design:	The protocol has a Cluster Randomized Controlled Trial design, with intra-subject and inter-subject evaluation, with two parallel groups: experimental and TAU control groups. With three measures, pre-test, post-test, and follow-up after three months. The participants will be four fifth-grade courses, aged 9 to 11. The allocation will be randomized by groups and not individually. The final sample will be a minimum of 44 participants. The primary measures will be neuropsychological tests to assess executive functions (cognitive flexibility, working memory, inhibitory control, and planning). Secondary measures will be a computational thinking test, neuropsychological tests to assess metacognition and attention, a sociodemographic questionnaire, and a satisfaction and adherence scale. The experimental group will participate in the COGNI-MACHINE computational thinking training designed by the first author. The intervention will occur at the educational institution twice a week in 60-minute sessions lasting 12 weeks and 24 sessions. The TAU control group will receive their computer science and technology classes as usual simultaneously and with the same hourly intensity. The evaluators taking the pre-test and post-test measurements will be blinded to the assignment. Moreover, the researchers in charge of the intervention will be blinded to the results of the evaluations.
Trial registration:	The study protocol was registered in International Standard Randomized Controlled Trial Number – ISRCTN, with registration number ISRCTN11380198.
Ethics:	The study protocol was submitted to the Research Ethics Committee of Universidad del Tolima and approved under act No.10 of December 13, 2022.

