**Fig. 1 fig0001:**
[figure not shown]
Layout of the experimental design. *Note:* RG1: Experimental group; RG2: Control group; On: Measure; X: Intervention.

For the intra-subject analysis, each group will be evaluated before starting the intervention (T1) and after the intervention (T2). Three months after the end of the intervention, a third follow-up measure (T3) will be applied to the experimental group to recognize the permanence of the effect over time. Once the post-test phase is over, the control group will receive the same training in computational thinking. For the intersubject analysis, the study will include an active control group in treatment as usual (Treatment-As-Usual - TAU), which consists of receiving the usual treatment in parallel to the experimental group and for the same time as the experimental group [[67], [68]].

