### Assignment

The intervention will take place in school contexts, and the sessions will be articulated to curricular work in the area of technology; for this reason, it will be necessary to work with naturally constituted school groups. Consequently, the researchers will not individually assign the subjects to the interventions (Experimental and TAU) but will perform cluster randomization. Studies use cluster randomization in circumstances where individual randomization cannot be achieved, so participants are randomized as groups of individuals or clusters [69]. Randomization will be done by an investigator from outside the study who will assign four sealed envelopes (one for each school group) to each intervention.

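### The 0.95 power in Table 2 is computed for independently allocated children, but the trial randomises four school classes and nothing allows for clustering

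*Protocol article*

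**What the plan says.** Under *Sample's size calculation*, the protocol article reports that "The G-Power projection suggested a group size of 22 children for a total sample of 44 children". Table 2 lists an effect size of 0.25 to 0.5 (metric not named), alpha 0.05, power 0.95, two groups ("1 experimental group and 1 TAU control group") and three measures ("Pretest, posttest, follow-up"). It has no row for number of classes, class size, ICC or design effect.

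Under *Assignment*, the investigators "will not individually assign the subjects to the interventions (Experimental and TAU) but will perform cluster randomization". *Recruitment* says that four fifth-grade classes of one public school will take part, about 100 children in all. The reasons given for that number are age ineligibility and dropout of about 15%; clustering is not among them. The specifications table puts the two facts next to each other: "The allocation will be randomized by groups and not individually. The final sample will be a minimum of 44 participants".

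Two further places matter. The text with Fig. 1 says that "a third follow-up measure (T3) will be applied to the experimental group to recognize the permanence of the effect over time". The *Statistical analysis plan* section names a mixed repeated-measures ANOVA with group as the between-subject factor and no term for class. The *Discussion* lists the lack of individual randomisation as a limitation but does not carry it into the sample size.

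**The concern.** A power figure belongs to a design and a test. Table 2 gives the figure for one design, and *Assignment* describes another. When whole classes are randomised, children in a class share a teacher, a timetable and their peers, so 44 children carry less information than 44 independent ones. The comparison between arms also rests on only four class means, which leaves two degrees of freedom.

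There are two consequences. If the analysis respects the classes, a null result would be read as coming from a 95%-powered trial when the true power may be far lower. If the analysis ignores the classes, as the ANOVA reads, most of the apparent power is kept, but the false-positive rate rises above 5%.

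**Working it through.** **Inputs from the article.** Alpha 0.05; 2 groups; 3 measures; effect size 0.25 to 0.5; N = 44; four classes; about 100 children before losses; dropout about 15%.

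**Inputs assumed.** Effect size is Cohen's f. Correlation between measures is 0.5 with sphericity (G*Power defaults). Classes split 2:2, inferred from four classes and two arms. ICC of the outcome change is 0 to 0.20; the article gives none.

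**Step 1. Reproduce the stated figure.** For the within-between interaction, λ = f²·N·m/(1−ρ), with df (k−1)(m−1) and (N−k)(m−1).

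- N = 44: λ = 0.0625 × 44 × 3 / 0.5 = 16.5; df 2 and 84; power 0.956.
- N = 42: λ = 15.75; df 2 and 80; power 0.946.

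So 44 is the smallest even total above 0.95. Other settings give different totals: f = 0.5 gives 14; two measures give 54; the between-group main effect gives 142 (f = 0.25) or 38 (f = 0.5). The match identifies the calculation as one for independent children with f = 0.25.

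**Step 2. Design effect.** DE = 1 + (n−1)·ICC, with n children per class. At N = 44, n = 11: DE is 1.5, 2.0 and 3.0 at ICC 0.05, 0.10 and 0.20, so the effective sample is 44/1.5 = 29, 44/2.0 = 22 and 44/3.0 = 15.

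**Step 3. Class-level test of the T1–T2 change.** T3 is described for the experimental group only, so T1–T2 is the contrast available in both arms. With two measures and ρ = 0.5, f = 0.25 is a difference of d = 1.0 SD in change, and f = 0.5 is d = 2.0. The test is a t test on class means with 4 − 2 = 2 df and noncentrality d·√(N/(4·DE)). For example, at N = 44 and ICC 0.05, it is 1.0 × √(44/6) = 2.71, giving power 0.34.

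**Step 4. Three-measure version, for a like-for-like comparison with Step 1.** F with 2 and 4 df and λ = f²·N·3/(0.5·DE). At N = 44, f = 0.25 and ICC 0.05, λ = 16.5/1.5 = 11.0 and power is 0.51.

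| Class-level power | ICC 0 | 0.05 | 0.10 | 0.20 |
|---|---|---|---|---|
| T1–T2, f = 0.25, N = 44 (11 per class) | 0.44 | 0.34 | 0.27 | 0.21 |
| T1–T2, f = 0.25, N = 84 (21 per class) | 0.66 | 0.43 | 0.33 | 0.23 |
| Three measures, F(2,4), f = 0.25, N = 44 | 0.67 | 0.51 | 0.40 | 0.29 |
| T1–T2, f = 0.5, N = 44 | 0.89 | 0.77 | 0.68 | 0.54 |
| Three measures, F(2,4), f = 0.5, N = 44 | 1.00 | 0.97 | 0.92 | 0.79 |

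The 21 per class comes from 100 × 0.85 = 85 children over four classes. A simulation of 200,000 runs gave the same T1–T2 values at f = 0.25 to within 0.003.

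**Step 5. What happens if class is ignored.** In the same simulation with no true effect, a child-level test of the T1–T2 change at a nominal 5% rejects in 11%, 17% and 28% of runs at N = 44 for ICC 0.05, 0.10 and 0.20. With 25 per class (N = 100), the rates are 19%, 30% and 44%.

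**The case against.** **The total of 44 is a minimum.** The article expects about 100 children before losses, so power at 44 is the low end. This stands, and the 84-child row is there for that reason. It lifts T1–T2 power to 0.66 at ICC 0, but only to 0.43 at ICC 0.05 and 0.23 at ICC 0.20, because the number of classes stays at four.

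**Part of the drop is not due to clustering.** This also stands. The stated figure is for three measures. With independent children and only T1–T2, power at N = 44 is already 0.90 (λ = 0.0625 × 44 × 2 / 0.5 = 11; df 1 and 42), not 0.956. A reader might infer that clustering alone takes power from 0.95 to between 0.2 and 0.45. The documents do not support that: the like-for-like three-measure range at N = 44 is 0.67 to 0.29, and any single range depends on an ICC that the article does not give.

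**Table 2 gives effects up to 0.5.** At that end the shortfall is smaller. T1–T2 power at N = 44 is 0.89 to 0.54, and the three-measure test exceeds 0.95 for ICC up to 0.05. But f = 0.5 is not the value that yields 44, and a three-measure comparison between arms needs T3 in both, which the text with Fig. 1 does not provide.

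**A separate analysis plan may handle clustering.** It might, for the analysis model. It cannot make the printed parameter table correct: the article gives its inputs and a resulting power, and these do not fit the stated allocation.

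A reader might also infer that the arithmetic is wrong. It is not; it reproduces exactly. What is wrong is the design that it describes.

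**Conclusion.** The point holds: the 0.95 in Table 2 applies to independently allocated children and not to four randomised classes. That conclusion rests on the exact reproduction of N = 44 and on the absence of any clustering allowance, and it does not depend on a particular ICC.

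The size of the shortfall is conditional on f = 0.25, correlation 0.5, a 2:2 split and ICC 0 to 0.20. At N = 44, both class-level tests shown fall short of 0.95 at f = 0.25 even with an ICC of zero, because so few degrees of freedom remain. At f = 0.5 the T1–T2 test also falls short. The child-level ANOVA does not rescue the figure, since it keeps its apparent power by giving up control of the type I error.

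A reader might go further and conclude that the trial must enrol more children or be relabelled as preliminary. The finding does not require either; what is wrong is the stated power.

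**What to change.** Remove the 0.95 from Table 2 and restate the table with:

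- four clusters and the split between arms, written out;
- expected analysed class size (11 at the minimum, about 21 as expected);
- an assumed ICC range, labelled as an assumption;
- the between-class degrees of freedom (2 for T1–T2);
- the metric of the effect size, the assumed correlation and the contrast to which the power refers;
- the resulting power, or the expected confidence-interval half-width, across the stated effect range.

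If a half-width is preferred for the T1–T2 change, it is 4.303 × √(ICC + (1−ICC)/n) in SD units of change. For n = 11 this gives 1.30 SD at ICC 0 and 1.59 SD at ICC 0.05.

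The abstract states no power, so no power figure there needs changing. The cost is a text amendment and a less favourable stated figure.

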### Statistical analysis plan

A hypothesis test will be conducted through Mixed Repeated Measures Analysis of Variance (ANOVA MR) with Bonferroni corrections to look at the differences between groups, in which the pre-test, post-test, and follow-up measures will be the factor of repeated measures. (Within-subject) and the difference between the experimental and control groups as the subject factor. The effect size will be measured with partial eta squared. The assumptions of this type of analysis assume a continuous metric-dependent variable with approximately normal distribution and with homoscedasticity in each of the groups.

A multivariate linear regression analysis will also be performed to assess the correlations between cognitive measures and computational thinking. And logistic regressions to analyze binary variables to evaluate the association between the covariates and the results.

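### Table 2's power of 0.95 at 44 children rests on three measures in both arms; the randomised pre/post comparison has about 0.90 on the same inputs, and the effect size has no named scale

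*Protocol article*

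**What the plan says.** In the protocol article, the section on sample size reports that "The G-Power projection suggested a group size of 22 children for a total sample of 44 children". Table 2 lists the inputs: effect size 0.25 to 0.5, described as "Data based on reports from previous studies"; alpha 0.05; power 0.95; two groups, "1 experimental group and 1 TAU control group"; and three measures, "Pretest, posttest, follow-up". It names no effect-size scale and no correlation between measures.

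The Statistical analysis plan section uses the same three time points as the within-subject factor of a mixed ANOVA, with arm as the other factor, and adds: "The effect size will be measured with partial eta squared".

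The text under Fig. 1 in Protocol design differs: "a third follow-up measure (T3) will be applied to the experimental group to recognize the permanence of the effect over time". It also says that controls get the training once post-test is over. The Control group section says the same, as a crossover after week 12.

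The Recruitment section expects about 100 children from four classes, with dropout of around 15%.

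**The concern.** A power figure describes one particular test. Table 2's figure belongs to a test that needs all three measures in both arms. The Protocol design section provides no control data at the third measure. By then the controls are also being given, or have had, the training, so even if they were measured the third time point would not compare training with usual classes. Only the first two measures carry that comparison, and a two-measure test at the same f has less power.

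The effect size adds a second difficulty. A value of 0.25 means very different things as Cohen's f, as a standardised mean difference or as partial eta squared. Without the scale, a reader cannot tell how large a benefit the trial is sized to detect, or whether the values taken from earlier studies were entered on the scale that the software expects.

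**Working it through.** **Inputs from the article:** two groups of 22 (N = 44), m = 3 measures, alpha 0.05, effect size 0.25 to 0.5, target power 0.95.

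**Assumed, because not stated:** the effect size is Cohen's f; the correlation between measures rho is 0.5 (the software default); sphericity holds; children are independent.

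**1. Reproducing the stated figure.** For the group-by-time interaction with two groups, lambda = f² × N × m / (1 − rho), with m − 1 and (N − 2)(m − 1) degrees of freedom.
- f = 0.25, m = 3: lambda = 0.0625 × 44 × 3 / 0.5 = 16.5 on 2 and 84 df; power 0.956.
- N = 42 gives 0.946, so 44 is the smallest balanced total that reaches 0.95.
- At f = 0.5 only 14 children would be needed, so 44 was set by the low end of the range.

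**2. The pre/post comparison, same f and rho.** With m = 2, lambda = 0.0625 × 44 × 2 / 0.5 = 11 on 1 and 42 df; power 0.900. Reaching 0.95 takes 54 children.

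**3. Sensitivity to rho (two measures, f = 0.25).** N = 84 stands for 100 children less 15% = 85, rounded down to balanced arms.

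| rho | Power, N = 44 | Power, N = 84 |
|---|---|---|
| 0.3 | 0.78 | 0.97 |
| 0.5 | 0.90 | 0.995 |
| 0.6 | 0.95 | 0.999 |
| 0.7 | 0.99 | >0.999 |

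**4. What f = 0.25 means here.** With two groups and two measures, a difference in gain of D standard deviations gives interaction cell effects of D/4, so f = D/4 and D = 4 × 0.25 = 1.00 SD. With three measures and the gain held at the third, f = D/√18, so D = 0.25 × 4.243 = 1.06 SD. As a check, a two-sample t test at d = 1.0 with 22 per arm also has power 0.900.

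**5. If 0.25 to 0.5 were standardised mean differences in change (an assumption).** At rho = 0.5 the SD of the change score is √(2 × 0.5) = 1, so raw SD and change SD coincide. The noncentrality is d × √(n/2), with n per arm.
- N = 44 (n = 22): d = 0.25 gives 0.829, power 0.13; d = 0.5 gives 1.658, power 0.37.
- N = 84 (n = 42): d = 0.25 gives 1.146, power 0.20; d = 0.5 gives 2.291, power 0.62.

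**The case against.** Much can be said for the plan, and most of it stands as a limit on the point.

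- **The arithmetic is not wrong.** Given its inputs, 44 is the correct answer. The fault lies in an input that the design contradicts and in an effect without a scale.
- **The correlation is unstated.** At rho = 0.6 the two-measure test reaches 0.95 with 44 children. That is a reason to state rho, but it does not rescue Table 2: at f = 0.25 and rho = 0.6 the three-measure calculation gives 0.985 at 44 and 0.980 at 42, so 44 would not have been the minimum.
- **Forty-four is a floor.** With about 84 analysed, the two-measure test at f = 0.25 has power 0.97 or more for rho of 0.3 and above. The 54 children lie well inside planned recruitment, though exclusions for age and for attendance below 70% could reduce the analysed number.

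A reader might infer that the trial is underpowered on any reading other than Table 2's. The documents do not support that. At f = 0.5, the top of the stated range, two-measure power exceeds 0.99. If 0.25 were itself a partial eta squared, the one effect measure that the article names, f would be √(0.25/0.75) = 0.577 and power at 44 about 0.95 or more.

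A reader might also apply the power of the between-group main effect, 0.51 at f = 0.25. The working hypothesis concerns how executive functions evolve over time, which is the interaction, so that test is not the one to judge by.

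Finally, a condensed article may leave details to a fuller document. Here the article prints the calculation with its inputs, and one of them conflicts with its own design section.

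**Conclusion.** The point holds in limited form. Table 2's power of 0.95 describes a three-measure comparison that the Protocol design section does not provide. For the randomised pre/post comparison the same inputs give 0.90 at the stated minimum of 44, with 54 needed for 0.95. This assumes f = 0.25, rho = 0.5 and sphericity; over rho from 0.3 to 0.7, power at 44 is 0.78 to 0.99. The loss is modest and would probably disappear at the expected recruitment if f = 0.25 is the true target.

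The missing scale has the larger potential effect. As f, the low end is a differential gain of about 1 SD. As standardised mean differences in change, the range would give power of 0.13 to 0.37 at 44 and about 0.20 to 0.62 at 84. Which scale the earlier studies used cannot be seen from the article, so these figures show what hangs on the omission and do not establish a mis-scaling.

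Every figure treats children as independent. Allocation is by class, with four classes, and any correlation within classes would lower them.

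**What to change.** Reconcile Protocol design, Table 2, the Control group section and the Statistical analysis plan section on who is measured at the third time point and what that measure is for.

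Then restate Table 2 for the pre-test to post-test contrast between arms:
- one effect value instead of a range, on a named scale, for example the difference in post-test score adjusted for pre-test, in SD units;
- the values from earlier studies converted to that scale before use;
- the assumed pre/post correlation;
- the resulting power at the minimum of 44 and at the number expected to be analysed.

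The cost is a recalculation and revised table text. No children are added. The downside is a less favourable stated power at the minimum size.

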### Recruitment

We evaluated the possible causes of loss from the sample: (1) subjects who did not meet the inclusion factors for the sample, especially the age of the children; (2) dropout rate for this school grade, which is usually around 15%; consequently, for the recruitment we decided to include 4 fifth grade school groups from the same public educational institution in the city of Ibagué, Colombia. Among the four courses, it is expected to convene approximately 100 children, so that the final sample for the analysis has the minimum projected size.

### Assignment

The intervention will take place in school contexts, and the sessions will be articulated to curricular work in the area of technology; for this reason, it will be necessary to work with naturally constituted school groups. Consequently, the researchers will not individually assign the subjects to the interventions (Experimental and TAU) but will perform cluster randomization. Studies use cluster randomization in circumstances where individual randomization cannot be achieved, so participants are randomized as groups of individuals or clusters [69]. Randomization will be done by an investigator from outside the study who will assign four sealed envelopes (one for each school group) to each intervention.

### Bias control

We used the Cochrane organization's control for bias tool for controlled trials [70] which covers six bias domains. Table 3 shows the actions established to control the appearance of the most common types of bias in non-clinical studies: selection, detection, performance, performance, desertion and reporting [71].

**Table 3 tbl0003:** Cochrane risk of bias check tool.

Bias		Description
Selection bias	Sequence generation	An investigator from outside the study will randomize the school groups to the interventions.
	Allocation concealment	A qualified evaluator outside the research group will be in charge of the evaluation. This evaluator will be blind to the group assignment and the nature of the intervention.
Performance bias	Blinding of participants and staff	The evaluator will be blind to the intervention. Since the control group will be treated as usual, blinding among the participating subjects will not be possible
Detection bias	Blinding of assessors to outcome.	The evaluators will be blind to the type of intervention applied. The investigator in charge of the intervention will be blinded to the results of the evaluation.
Attrition bias	Incomplete outcome data.	Data from participants who complete less than 70% of the training will be excluded from the study. We will perform data imputation; for this, we will evaluate the difference of the results with the data of the excluded subjects and without them.
Reporting bias	Selective reporting of results	We will present the results in accordance with the objectives set out in the trial registration.

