### Inclusion and exclusion criteria

This study will include children in fifth grade of primary school between 9 and 11 years old. Table 1 contains the criteria for including data from children in the controlled trial.

**Table 1 tbl0001:** Inclusion and exclusion criteria.

Inclusion criteria	Exclusion criteria
1. Children of both sexes.	1. Children with uncorrected sensory impairment.
2. Children who at the time of the beginning the study are between 9 and 11 years old.	2. Children with a psychiatric diagnosis.
3. Children enrolled in fifth grade of primary school in an educational institution of Ibagué, Colombia.	3. Children who exceed the age range at the beginning of the pre-test.
4. Children with typical cognitive development.	4. Children with previous experience in computational thinking, coding or programming training.
5. Children who have participated in 70% of the intervention.	5. Children who have joined the educational institution after the application of the pretest.

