### Interventions

#### Experimental group

The experimental group will participate in a training in computational thinking called COGNI-MACHINE, designed by the first author. The intervention comprises 24 sessions; each session will be structured as a workshop and will take place in the computer room of the participating educational institution. The intervention will last 12 weeks, with two sessions per week of 60 min each.

The training workshops will be based on the principles of problem-based learning, and the activities will be designed following the principles of low floor / high ceiling. For the design of the computational thinking intervention, the following sources were taken into account: (1) The recommendations emerging from the results of the previously conducted pilot test [[30], [45]]; (2) A broad review of activities, projects, and courses available to teach computational thinking in school contexts; (3) A systematic review of background and similar studies.

To select the plugged and unplugged activities that would be part of the training, we reviewed: (1) Existing open-access training and existing repositories of unplugged activities; (2) The integrated development environments available to learn to code in blocks; 3) The educational robotics devices available in the market for Colombia. From these reviews, unplugged activities were selected from different sources such as CS Unplugged, code.org, programemos.com, and Mintic's “Coding for kids” [88]. Lessons from courses B, C, and D of the code.org integrated development platform and the Makecode integrated development platform were selected for the block programming activities. For the plugged projects, he selected the micro:bit V2 microprocessor (see Fig. 2), which is a small programmable board designed by the BBC which has several integrated sensors, Bluetooth connection, radio frequency, push buttons, and LED light outputs.

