#### Control group

The control group at TAU will receive the traditional Technology and Computer Science classes 2 hours a week for 12 weeks. In these classes, students will learn to use Microsoft Office applications. After the 12 weeks of intervention, a crossover design will be conducted so that the control group participates in the same intervention as the experimental group and the experimental group participates in the 12 weeks of traditional technology classes.

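### The 70% attendance rule selects the analysed children on behaviour after allocation, so the stated analysis set is not the groups as randomised

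*Protocol article*

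**What the plan says.** Two places in the protocol article set the rule.

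- **Inclusion and exclusion criteria, Table 1**, inclusion criterion 5: "Children who have participated in 70% of the intervention". The sentence introducing the table gives its purpose: "Table 1 contains the criteria for including data from children in the controlled trial". So the table decides whose data are analysed as well as who is approached.
- **Bias control, Table 3**, attrition-bias row: "Data from participants who complete less than 70% of the training will be excluded from the study". The same row then announces imputation and says "we will evaluate the difference of the results with the data of the excluded subjects and without them".

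On the two arms:

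- **Experimental group:** "The intervention comprises 24 sessions".
- **Control group:** these children "will receive the traditional Technology and Computer Science classes 2 hours a week for 12 weeks". No attendance threshold is stated for those classes, and the control children receive the computational thinking programme only after the post-test.

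On allocation, the Assignment section says that "the researchers will not individually assign the subjects to the interventions (Experimental and TAU) but will perform cluster randomization". The Statistical analysis plan section specifies a mixed repeated-measures ANOVA and names no analysis population.

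**The concern.** Whether a child reaches the threshold cannot be known when the classes are allocated. It depends on what happens over the following 12 weeks, including how the child responds to the programme. A criterion of that kind cannot define eligibility. Using it to decide whose data count gives up the comparison that randomisation protects. It is listed as the control for attrition bias, but it adds avoidable attrition to whatever occurs naturally.

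The rule applies to every primary outcome. If children who attend often also gain more, for reasons such as motivation, health or family support, the kept children are not comparable with the full classes on the other side. The rule also removes the children who tell most about adherence and feasibility, which Table 5 lists among the secondary outcomes.

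**Working it through.** **1. The cut-off.** 0.70 × 24 sessions = 16.8, so a child needs at least 17 sessions to be kept.

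**2. The planned sample size, reproduced first.** Sample's size calculation, Table 2, gives α = 0.05, power 0.95, two groups, three measures, effect size from 0.25, and N = 44. For a within-between interaction, with effect size read as f = 0.25 and with correlation 0.5 and sphericity assumed (not stated in the article):

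- λ = f² × N × m / (1 − ρ) = 0.0625 × 44 × 3 / 0.5 = 16.5
- df = 2 and (44 − 2) × 2 = 84
- power = 0.956, and 44 is the smallest even N that reaches 0.95.

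The figure reproduces. Recruitment expects about 100 children. After a 15% loss, 100 × 0.85 = 85 remain, well above 44. The exclusion is not needed to reach the planned size, and dropping it costs no sample.

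**3. Bias from excluding children in one arm.** Let p be the share excluded, and K and E the mean gains (post-test minus pre-test) of kept and excluded children.

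- Mean gain of all children = (1 − p)K + pE
- Bias = K − [(1 − p)K + pE] = p × (K − E)

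Gain is the right quantity because the hypothesis concerns differences in evolution and the test is group by time. If kept children simply score c higher at both pre-test and post-test, the kept mean shifts by p × c at both times and the difference between times is unchanged. Only a gap in gain matters.

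**4. Size, as an assumption only.** The documents give neither p nor the gap.

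| Share excluded | Gap in gain | Bias |
|---|---|---|
| 10% | 0.3 SD | 0.10 × 0.3 = 0.03 SD |
| 25% | 0.5 SD | 0.25 × 0.5 = 0.125 SD |

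**5. If the rule covers both arms.** The net bias is p₁ × gap₁ − p₀ × gap₀ (experimental minus control). It is zero if shares and gaps are equal, and otherwise can take either sign. The two programmes differ in content, so equality cannot be presumed.

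**6. A second illustration, also assumed.** Suppose there is no true effect, the lowest attenders are dropped in the experimental arm only, attendance correlates r with gain, there are 50 children per arm before exclusion, and clustering is ignored. The shift, in SDs of gain, is r × φ(z_q) / (1 − q) for share q dropped. The nominal two-sided error is 0.05.

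| q | r | Shift | Type I error |
|---|---|---|---|
| 10% | 0.2 | 0.039 | 0.054 |
| 10% | 0.5 | 0.097 | 0.076 |
| 20% | 0.2 | 0.070 | 0.063 |
| 20% | 0.5 | 0.175 | 0.131 |

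The distortion ranges from negligible to material, depending on inputs that the article does not supply.

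**The case against.** **Which arm is filtered.** A reader might infer that attenders in the experimental arm are compared with all controls, so that the bias is one-sided and upward. That is the more natural reading, because the word training mostly names the experimental programme and no attendance rule is given for the control classes. The text does not establish it. Table 1 speaks of children in the trial without naming an arm, the Assignment section calls both conditions interventions, and the hypothesis describes the control condition as a conventional training programme. Taken literally as the experimental programme alone, criterion 5 would exclude every control child at post-test, so the one-sided reading also bends the text. This part of the objection stands: direction is not established. The departure from the groups as randomised remains either way.

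**The 15% figure.** It is tempting to use it as the share excluded. Recruitment describes it as the "dropout rate for this school grade, which is usually around 15" per cent. That is loss from the grade, so it affects both arms, and it is not the share attending under 70% of sessions. It does not belong in the bias formula.

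**Lower-scoring absentees.** It is also tempting to say that bias follows if absentees score lower. For the group-by-time test a stable difference in level cancels, as shown above. This too stands.

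**The problem is already partly handled.** Table 3 commits to imputation and to comparing results with and without the excluded children, and a separate analysis plan might name a primary population. The comparison is a genuine safeguard, since a marked distortion would show. But the article does more than leave the population open: it states an exclusion rule and an inclusion criterion. A comparison that follows them does not make the as-randomised result primary. It also requires post-test data from low attenders, and the article does not say these will be collected.

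**Conclusion.** The point holds. As written, the analysis set is selected on attendance after allocation and is not the groups as randomised. This follows from the two stated rules and needs no assumption.

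The size and direction of the bias are not established. A bias of about 0.03–0.13 SD requires exclusion in one arm only, 10–25% excluded, and a gap in gain of 0.3–0.5 SD; all three are assumptions. If the rule covers both arms, the comparison is attenders against attenders in two different programmes, and the net bias could be smaller or of either sign. The documents do not support a claim of known upward bias against an unfiltered control arm.

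**What to change.** 1. Delete inclusion criterion 5 from Table 1 and the exclusion sentence from the attrition-bias row of Table 3.
2. Define the primary analysis set as all otherwise eligible children in the four classes at pre-test, analysed in the arm their class was allocated to, whatever their attendance.
3. State that post-testing (T2) will be attempted for every such child, including low attenders.
4. Handle missing T2 with the imputation already planned, or with a likelihood-based mixed model in place of an ANOVA that normally needs complete cases.
5. Keep the 70% subset as a labelled per-protocol sensitivity analysis, and state which arm or arms the rule covers and how attendance is counted in each.

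Cost: items 1, 2 and 5 are wording. Item 3 needs some extra testing effort, though the children are in the same school. Item 4 is a change of method only if the mixed model is chosen. The estimate may be slightly diluted by non-attendance, because it then describes the effect of offering the programme to a class.
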